### Consent

Prior to participation in a beta test or pilot trial, all participants (ie, clients and PRCs) will complete the informed consent process during a meeting scheduled with a member of the research team. A team member will review the consent form with participants, who will be given adequate time to ask questions before deciding to participate. Consent will be documented via virtual signature in REDCap, wherein participants indicate their agreement and enter a unique study ID number assigned to them by the research team. Consenting online is a common practice in minimal-risk social behavioral research. Although the study procedures do not involve collecting data from the EHR, client participants will also sign a HIPAA authorization, as the research team will encounter identifying information through surveys and review of client data collected by PRCs. For the beta test phase, the study team will request that participating PRCs also attend their clients’ meetings, although PRCs will exit the room (virtual or physical) during the actual consent process. During this meeting or a separate meeting after consent has been obtained, all participants will be instructed on how to install and uninstall the app, and the process to connect the PRC and client within the app will be completed, along with brief training on the functions and resources available within the app.

### Participant Incentives

Client participants are compensated via an electronic gift card after completion of each qualifying study activity. PRCs complete study activities during normal work hours and do not receive additional compensation. Table 6 illustrates the maximum compensation clients could obtain.

**Table 6. T6:** Maximum compensation for participation in each phase of research.

Phase	Surveys		Stakeholder engagements (including interviews)		Total (US $)
	Count	Compensation (US $)	Count	Compensation (US $)	
Beta test	4	$15/survey	1	$25/engagement	$85
Pilot	12	$15/survey	1	$25/engagement	$205

Compensation amounts reflect the time and effort commitment required of participants. It is expected that each survey will take 5‐10 minutes to complete, though some could take up to 60 minutes. Interviews will last approximately 30 to 60 minutes. Estimated time spent using Peer PLUS during their trial period will vary. As such, for the beta tests, we anticipate that participants may spend up to 3 hours taking surveys and participating in an interview, not including travel, and for the pilot, this may be up to 10 hours.

### Beta Testing Procedure

During each beta test, PRCs and clients were instructed to use the platform for the asynchronous communication that would occur as part of their existing support relationship; that is, participants were encouraged to use the app if they liked it and felt that it met their needs, but there was no minimum amount of app usage required for participation. PRCs were instructed to use the client management system for documentation. Participants were surveyed at regular intervals during their period of usage (eg, 15 and 30 days postenrollment) to assess perceptions on ease of use (SUS and/or our custom user experience survey; refer to Textbox 2).

At the end of each beta test, we applied UCD methods (eg, contextual inquiry and think-aloud exercises) in stakeholder engagements with enrolled participants to further establish usability issues and facilitate rapid evaluation to inform app and tool kit refinement. This included both virtual and in-person meetings where the team asked specific questions following up on their individual use patterns, doing think-aloud walk-throughs of the mobile app features, and rank weighting of feature changes. The findings from these sessions were collated and presented back to the research team for discussion and potential translation into the next iteration of the platform. During this process, we used RE-AIM Planning and Evaluation Framework constructs [38] to identify implementation barriers and ERIC strategies [40] and UCD methods to resolve them.

### Pilot Procedure

During the pilot study, PRCs and clients will again be asked to use the platform for asynchronous communication and will be surveyed about their experience. Postenrollment surveys will be deployed at multiple time points: quality of working alliance (WAI-SR) will be assessed twice (eg, 30 and 60 days), and perceptions on ease of use (SUS and/or our custom user experience survey) will be assessed at 2 time points (eg, 20 and 80 days). Clients will additionally be queried on self-reported recovery outcomes (SURE) at baseline and at up to 3 time points post enrollment (eg, 30, 60, and 90 days), and on client experience (ECHO) up to 2 times (eg, 30 and 60 days).

We will additionally conduct semistructured interviews with a subset of clients and PRCs, applying UCD methodology and focusing on perceived usefulness and relative advantage of the Peer PLUS platform. An example interview guide is provided in Multimedia Appendix 1. We will conduct post-pilot ethnographic observations with PRC and manager participants to note changes in workflows as a result of the platform (eg, distribution of resources and report generation).

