### Aims and Contributions

In this study, we propose a robust “in-the-wild” evaluation of our novel technology tool by the platform’s intended users—PRCs and their clients—to assess its usability and its impact on specific client-centered recovery outcomes. Based on the findings of this real-world testing, we will subsequently refine the platform design and develop an implementation tool kit for future deployment. Specific study aims are displayed in Table 2.

**Table 2. T2:** Aims and milestones to be accomplished by the end of the R21 study period.

Aims and objectives	Milestone
Aim 1: Determine if Peer PLUS^a^ is perceived as usable and has sustained use by PRCs^b^ and their clients.	
Refine: Apply UCD^c^ methods and RE-AIM^d^ [38] to refine Peer PLUS and develop an implementation tool kit.	Revised Peer PLUS app Draft implementation tool kit
Usability and feasibility: Validate that Peer PLUS is easy to use and determine if it is likely to have uptake and sustained use in the proposed R33 phase.	Clients and PRCs evaluate Peer PLUS with an average SUS^e^ [44] ≥68 25% of clients approached to participate in the pilot will have a smartphone and consent to participate PRCs connect to clients who are using Peer PLUS 20% more than clients who are not
Aim 2: Evaluate the potential impact of Peer PLUS on recovery, quality of care, and therapeutic alliance between clients and their peer recovery coach during care for SUD^f^.	
Impact: Demonstrate Peer PLUS impact and ability to robustly evaluate the app in the proposed R33 phase.	The following metrics are collected from all clients participating in the pilot SURE^g^ [45] CAHPS^h^ ECHO^i^ [40] WAI-SR^j^ [46,47]

a PLUS: People Leveraging Urgent Support.

b PRC: peer recovery coach.

c UCD: user-centered design.

d RE-AIM: Reach, Effectiveness, Adoption, Implementation, and Maintenance.

e SUS: System Usability Scale.

f SUD: substance use disorder.

g SURE: Substance Use Recovery Evaluator.

h CAHPS: Consumer Assessment of Healthcare Providers and Systems.

i ECHO: Experience of Care and Health Outcomes.

j WAI-SR: Working Alliance Inventory.

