### Statistical Analysis Plan

Data will be analyzed at the aggregate level. To address aim 1 (usability and potential for sustained use), descriptive statistics will be computed on the SUS and recruitment rates to assess whether feasibility targets are met (ie, SUS score ≥68, 25% client eligibility and recruitment rate). Using data collected from the Peer PLUS user log, we will conduct a general categorical analysis as a proxy for end-user engagement. To assess our primary outcome related to client contact, in the pilot trial, we will compare the number and rate of connections to clients using the platform to PRCs’ documentation of contact with nonparticipating clients to determine whether the target of 20% more contacts with enrolled clients was met. Further, to address aim 2 (evaluating the impact of Peer PLUS on treatment-related outcomes), descriptive statistics will be calculated for the SURE, CAHPS ECHO, and WAI-SR survey measures deployed during the pilot trial, which will demonstrate potential improvement related to recovery, quality of care, and therapeutic alliance, as well as the feasibility of using these measures to evaluate the app in the R33 phase.

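### WAI-SR and ECHO have no pre-app value and no comparator in the pilot, so they cannot show the improvement in alliance and quality of care that the plan expects of them

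*Protocol article*

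**What the plan says.** **Schedule.** Under Pilot Procedure, the alliance measure for clients and peer recovery coaches (PRCs) is post-enrollment only: "quality of working alliance (WAI-SR) will be assessed twice (eg, 30 and 60 days". Clients are also surveyed "on client experience (ECHO) up to 2 times (eg, 30 and 60 days". The same paragraph treats SURE differently: "Clients will additionally be queried on self-reported recovery outcomes (SURE) at baseline and at up to 3 time points post enrollment".

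**Start of exposure.** Under Consent, at the consent meeting or a separate meeting after it, "all participants will be instructed on how to install and uninstall the app". Client and PRC are connected in the app and trained at that time.

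**Who completes the measures.** Table 5 has up to 40 pilot clients using the app and completing WAI-SR, SURE and ECHO, and up to 15 PRCs completing WAI-SR. According to Table 4 and the Statistical Analysis Plan section, nonparticipating clients supply nonidentifying descriptive data and documented contacts. They complete no outcome survey.

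**Stated inference.** The Statistical Analysis Plan section says that "descriptive statistics will be calculated for the SURE, CAHPS ECHO, and WAI-SR survey measures deployed during the pilot trial". From these summaries alone it draws a conclusion about all three domains: "which will demonstrate potential improvement related to recovery, quality of care, and therapeutic alliance". Table 2 (Aims and Contributions) words the Aim 2 objective as "Demonstrate Peer PLUS impact and ability to robustly evaluate the app in the proposed R33 phase". Principal Findings hypothesizes stronger alliance and better outcomes on SURE, ECHO and WAI-SR from use of the app.

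**The concern.** Improvement is a change from a reference value. SURE has one. WAI-SR and ECHO have neither a value from before the app nor a group without it, yet the plan draws the same conclusion from all three. An analysis plan cannot repair this, because a value that was not collected cannot be recovered.

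The missing interval also matters to the sponsor. Eligibility Criteria restricts the pilot to clients within 6 months of program entry, because beta feedback pointed to the app's usefulness in forming the PRC-client relationship early in treatment. If the app has an early effect on alliance, part of it will have occurred before the first WAI-SR. What remains visible is mixed with the growth that a young relationship would show without the app. A reader could take a rise from day 30 to day 60 as an app effect, or take a flat line as no effect, and neither conclusion would be justified.

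**Working it through.** The document gives no power, alpha, SD or effect size for WAI-SR or ECHO, so there is no figure of that kind to reproduce. The check is a count, followed by two illustrations whose assumptions are not in the documents.

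**1. Count of reference values** (Pilot Procedure, Consent, Tables 4 and 5)

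| Measure | Before app use | After enrollment | Comparison groups |
|---|---|---|---|
| SURE | 1 | up to 3 | 0 |
| WAI-SR | 0 | 2 | 0 |
| ECHO | 0 | up to 2 | 0 |

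The day numbers are examples, but neither measure is described at any point as taken at baseline. For ECHO even the day 30 to day 60 contrast is not assured, since the schedule says up to two times.

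**2. How much change the day 30 to day 60 window could hold.** Assume that scores approach a plateau exponentially with half-life h days, so f(t) = 1 − 2^(−t/h). The share of the day 0 to 60 change that falls in days 30 to 60 is [f(60) − f(30)] / f(60) = x/(1 + x), with x = 2^(−30/h).

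- h = 7: 5%
- h = 14: 18%
- h = 30: 0.5/1.5 = 33%
- h = 60: 0.707/1.707 = 41%

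Under this shape the window always holds less than half of the change, and very little of it if the effect is quick.

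**3. What a baseline would give.** For mean within-client change, the 95% CI half-width in SD units is t(0.975, n−1) × √[2(1−ρ)] / √n. It assumes equal SDs at both times and independent clients, which ignores sharing of PRCs.

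- n = 40, ρ = 0.5: 2.02 × 1.00 / 6.32 = 0.32 SD
- n = 40, ρ = 0.3 and 0.7: 0.38 and 0.25 SD
- n = 20, ρ = 0.3, 0.5 and 0.7: 0.55, 0.47 and 0.36 SD

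**4. Survey count against Table 6.** The plan's own total reproduces: 12 × $15 + $25 = $205. The listed client surveys are WAI-SR 2 + SUS/custom UX 2 + SURE 4 + ECHO 2 = 10 if SUS and UX count as one, or 12 if they are separate. Two added baseline instruments, paid as separate surveys, bring this to 12 ($205) or 14 (14 × $15 + $25 = $235). The added items number 12 (WAI-SR) + 6 (ECHO) = 18.

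**The case against.** The case on the other side is substantial, and much of it limits the point.

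- **A reader might infer that Aim 2 or the R33 decision fails.** The documents do not support that. The Aim 2 milestone in Table 2 is only that the three metrics are collected from pilot clients, and the schedule can meet it. The go/no-go targets are a SUS score of at least 68, 25% recruitment and 20% more contacts. None uses WAI-SR or ECHO.
- **A reader might infer that R33 loses inputs it needs.** The Results section names SURE as the R33 primary outcome, and SURE has a baseline here. Nothing says that R33 will be sized or analyzed on WAI-SR or ECHO change. The pilot would still yield their SDs, completion rates and a day 30 to day 60 correlation.
- **The wording is hedged.** The aim speaks of potential impact, and the analysis section of potential improvement and of the feasibility of using the measures. Feasibility can be shown on this schedule. The hedge does not rescue the claim about improvement, because even potential improvement needs a reference value.
- **A baseline would not allow attribution.** This is correct. Without a control group, natural growth of the relationship stays in the estimate.
- **A baseline may reflect a short relationship.** Recruitment Methods speaks of trust in the program, not of an established bond with the PRC. The items can be answered at enrollment, since clients must already receive PRC support, but some answers will rest on little contact.
- **Table 4 might be read as contradicting the baseline SURE**, because it lists SURE only under post-enrollment surveys. That column names the data source. At most the label needs clarifying.

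**Conclusion.** The concern holds in a limited form. For WAI-SR (clients and PRCs) and ECHO (clients), the pilot has 0 pre-app assessments and 0 comparators. Descriptive statistics on these two of the three Aim 2 measures can show levels and a change between about day 30 and day 60. They cannot show improvement in alliance or quality of care, and they cannot demonstrate impact. SURE can show change from baseline, but that change is also uncontrolled.

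The counts rest on the text alone. The statement that the first scores come after roughly a month of access rests on the example days and on set-up following consent promptly. The 5% to 41% shares and the CI half-widths are illustrations under assumed curves and correlations.

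This should be fixed, but it is not critical: no milestone, primary outcome or go/no-go target depends on it.

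**What to change.** 1. **Clients still to be enrolled:** give WAI-SR (client and PRC) and the 6-item ECHO subscale at the same session as the baseline SURE, before the app is activated. Report within-client change from baseline with 95% confidence intervals.
2. **Clients already enrolled without a baseline:** report levels only.
3. **In either case, change the wording** of the Aim 2 objective in Table 2, the Aim 2 sentence in the Statistical Analysis Plan section and the hypothesis in Principal Findings. They should say that these measures describe levels, uncontrolled change and feasibility for R33, not improvement or impact attributable to the app. If no baseline is added, this rewording alone removes the contradiction.
4. Clarify in Table 4 that SURE includes a baseline.

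**Cost.** A minor IRB amendment and 18 more short items at a survey session that already exists. If the two instruments are paid as separate surveys, up to $30 more per client. That stays within the $205 maximum if SUS and custom UX count as one survey, and reaches $235 if they are already counted separately. Pilot recruitment began in August 2025, so the baseline may cover only part of the sample, with wider intervals accordingly (about 0.47 SD at n = 20 against 0.32 SD at n = 40, for an assumed correlation of 0.5).

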### Platform and Implementation Tool Kit Development and Refinement

The protocol was designed to allow for iterative refinement of the Peer PLUS platform based on feedback elicited in each study phase. For example, ethnographic observations highlighted the need to digitize a variety of paper-based resources so that they could be easily shared within the app. Based on beta testing findings, the platform was enhanced considerably. Examples include streamlining the login process by allowing the email address (login ID) to be saved and not having to be reentered each time the app is opened, allowing more than 1 PRC to be attached to a client, and creating alerts in the client management system for individuals such as maternal clients who were timing out of being a maternal patient, allowing for a more seamless transition to a nonmaternal PRC if desired by the client. Findings of the postpilot trial interviews and observations will be leveraged to refine the app and update user guides, workflows, and other items for the implementation tool kit as needed.

The implementation tool kit will similarly be developed iteratively throughout study phases, leveraging findings and feedback, with the ultimate intent of facilitating seamless integration of Peer PLUS for other organizations. The tool kit will include recommended departmental policies to consider, instruments and UCD methods to apply in advance of Peer PLUS adoption to understand the unique context and workflow, instruments to evaluate implementation success, and user guides. This approach is intended to provide the necessary information for end users (including both clients and recovery staff) as well as other relevant stakeholders (eg, organizational technology support specialists) to use when implementing this platform into clinical workflows. Resources may include frequently asked questions, detailed instructions for use (eg, screenshots), definitions of terminology, and other information that facilitates understanding of what to expect during this process.

### Ethical Considerations

The study protocol and all applicable documents and amendments were approved by the Parkview Health Institutional Review Board (PRC21-0707 PLUS). The minimal risks associated with participation are outlined in the consent form, which all participants will electronically sign prior to participation in a beta test or pilot during the informed consent process detailed in the “Consent” section above. IRB-approved scripts will be used during recruitment and consent processes to describe study procedures, rights as research participants, and compensation. Participants will be compensated between US $15 and US $25 per study engagement, as approved by the IRB and described further in the “Participant Incentives” section above. Due to the sensitive nature of health data and the vulnerable population included in this study, measures will be taken to protect participants’ privacy and confidentiality, including storing data securely, coding participant data with unique identifiers stored separately from a password-protected code key, and encrypting exchanges of data between participant devices and the server to prevent unauthorized interception. The client management system is not available for download and follows data safety protocols as established by the health system. The mobile app will undergo extensive penetration testing by a third party to identify any security issues prior to the pilot launch. Issues identified will be addressed prior to PRC and client use of the app. During the study, access to the Peer PLUS mobile app will be restricted to participants and the research team; researchers will not review messages exchanged by participants. If a participant leaves the study for any reason, their access to Peer PLUS will be removed. If a PRC withdraws, their clients will be offered the option to either withdraw or be reassigned to another participating PRC, who will have access to all information visible to their previous PRC. Any data or findings shared outside of the research team will be deidentified and/or aggregated. Additional measures to protect participant safety are detailed under “Safety Protocols” below.

### Safety Protocols

Given the complexity of the SUD recovery journey, it is possible that participants may experience emotional discomfort when discussing or reflecting on their experiences during surveys or interviews. To minimize this risk, participants will be informed that participation is voluntary and they may decline to answer any questions. The consent form also outlines safety protocols that will be followed in relation to mental health concerns or other emergent situations. If a client expresses discomfort during a study engagement, researchers will refer them for follow-up with their PRC, as they will continue to receive standard-of-care treatment. Additionally, the research team will distribute a resource guide to each participant at enrollment with contact information for both local and national mental health helplines and facilities; this list of resources will also be accessible within the Peer PLUS platform. If during their period of participation clients do not receive a response from their PRC through Peer PLUS, or if they are having a medical emergency, they will be instructed to reach out as applicable to one of these additional resources. If a participant expresses suicidal thoughts, researchers will direct them to the health system’s 24/7 hotline as well as the Suicide and Crisis Lifeline (988). Further, all research team members have completed QPR suicide prevention training. Although participation itself is not expected to have physical health risks, clients in recovery are vulnerable to emergent situations. In the case of an adverse health event during a study engagement, emergency health services will be called. Client participants may also be withdrawn from the study if their PRC believes it is not in their best interest to continue.

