### Beta Testing and Pilot Trial

#### Sample Size and Planned Recruitment Rate

We planned to conduct up to 3 incremental beta tests of Peer PLUS, with up to 4 PRCs and up to 4 clients per PRC (n=16 clients) per test. After beta testing is completed, up to 15 PRCs and up to 40 clients will pilot Peer PLUS, which is in line with HCI testing practices [53]. After each test phase, select clients and PRCs will participate in stakeholder engagements to reflect on their experiences. The PRC manager will be involved throughout all phases of the study; in the context of our existing collaborative relationship, the manager has provided design input and serves as an intermediary between the research team and PRCs rather than being enrolled as a consented participant. However, the protocol was written to allow for manager participants (eg, in the case of changes to staffing or location). In total, up to 4 PRC managers, 16 PRCs, and 88 clients may participate across both phases; refer to Table 5.

**Table 5. T5:** Maximum number of participants per study activity.

	Peer PLUS^a^ use	Stakeholder engagements	Surveys		
			WAI-SR^b^	SUS^c^ and/or Custom UX^d^	SURE^e^ and ECHO^f^
Each beta test					
Clients	16	8	—^g^	16	—
PRCs^h^	4	4	—	4	—
PRC managers or supervisors	4	4	—	4	—
Pilot					
Clients	40	8	40	40	40
PRCs	15	15	15	15	—
PRC managers/ or supervisors	4	4	—	4	—

a PLUS: People Leveraging Urgent Support.

b WAI-SR: Working Alliance Inventory.

c SUS: System Usability Scale.

d UX: user experience.

e SURE: Substance Use Recovery Evaluator.

f ECHO: Experience of Care and Health Outcomes.

g Not applicable.

h PRC: peer recovery coach.

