Ethnographic methodology was applied due to its increasingly recognized value within the field of implementation science [59], allowing the research team to more thoroughly understand the context in which the platform would be deployed and informing its initial design. Through this, we identified a wide range of “invisible” work tasks completed by PRCs and devised a technological solution that would streamline these processes. Much of the day-to-day work of PRCs was not centrally documented or easily summarized, existing outside what is captured in existing literature [60,61] and furthering the lack of understanding surrounding the important nature of this role and emphasizing the need for a technological tool to mitigate these tensions. To this point, we integrated a PRC checklist from the literature [62], and throughout the beta and pilot studies will obtain feedback during the participant engagements on what is working and what is missing. At the culmination of the pilot test, we will identify changes in workflows resulting from using the technology, which is an integral aspect of iterative design and implementation processes [63].

By combining UCD and implementation science, we make a unique contribution to both fields within the context of digital health, enhancing existing implementation frameworks to accelerate the design, adoption, integration, and sustained effect of health technologies [37,41,42]. The clinical contribution of this project is 3-fold. First, it meets a need to improve the quality of aftercare among a population that faces a unique set of serious challenges related to their health condition, including stigma, chronicity, and potential for overdose death. Second, it tests a novel digital solution that captures dynamic processes of aftercare treatment, an integration model that can be generalized to other conditions wherein aftercare is a key component of client recovery. Third, it examines the feasibility of using informal communication data to further discern the impact of PRCs from other treatment modalities that occur in parallel, providing important data to support the necessity of these programs.

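### The safety section sends a client with a medical emergency to a guide described only as mental health contacts; it should send them to emergency health services

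*Protocol article*

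**What the plan says.** All the relevant procedure is in the Safety Protocols section of the protocol article.

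- **Resource guide.** Each participant receives a guide at enrollment with "contact information for both local and national mental health helplines and facilities". The same list is available in the app.
- **What clients are told.** The next sentence names two triggers. The first is that the PRC does not answer in the app. The second trigger, and the action for both, read: "or if they are having a medical emergency, they will be instructed to reach out as applicable to one of these additional resources".
- **Suicidal thoughts.** Researchers direct the participant to the health system's round-the-clock hotline and to the national crisis line.
- **Adverse health events.** "In the case of an adverse health event during a study engagement, emergency health services will be called".
- **Consent form.** "The consent form also outlines safety protocols that will be followed in relation to mental health concerns or other emergent situations". The form itself is not shown.

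The section also states that "clients in recovery are vulnerable to emergent situations".

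**The concern.** The two triggers need different responses. A client whose PRC has not replied needs another source of support, and a list of mental health contacts serves that purpose. A client with a medical emergency needs emergency medical care, which a mental health helpline does not provide. Joining the two in one sentence gives both the same destination, and that destination is wrong for the more dangerous case.

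Such an emergency is foreseeable. The safety section itself acknowledges the vulnerability of these clients, and the Discussion (Principal Findings) lists the challenges this population faces, "including stigma, chronicity, and potential for overdose death". The fallback instruction also carries weight because clients use the app on their own, communication is asynchronous (Intervention), and researchers do not read the messages (Ethical Considerations).

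If the wording is reused in user guides or policies for the implementation tool kit, which is still being developed for other organizations, the error would travel with it.

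**Working it through.** There is no plan figure to reproduce. The check is a reading of the safety section, sentence by sentence, followed by a search of the rest of the article for any route to emergency care that a client is told to use.

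**Step 1. What the instruction points to.** The sentence sends clients to additional resources just mentioned. The sentence before it describes the enrollment guide, and that guide is the only set of resources available as an antecedent. Its stated content is mental health helplines and facilities; no emergency medical service is named.

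**Step 2. Whether another rule covers the case.** The section's routes, side by side:

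| Situation | Who acts | Destination stated |
|---|---|---|
| No PRC response through the app | Client | Resource guide (mental health contacts) |
| Medical emergency | Client | Same resource guide |
| Discomfort during a study engagement | Researcher | Follow-up with the PRC |
| Suicidal thoughts expressed | Researcher | Hotline and national crisis line |
| Adverse health event during a study engagement | Not stated (services are called) | Emergency health services |

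Only the last row reaches emergency health services, and it is limited to study engagements. It does not cover a client using the app in daily life, which is the situation the second row addresses. The second and last rows do not contradict each other, because they apply in different settings. The problem is the destination in the second row.

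**Step 3. The rest of the article.** No other section tells a client with a medical emergency to contact emergency services.

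**Step 4. Exposure.** Inputs:

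- Pilot size: "up to 15 PRCs and up to 40 clients will pilot Peer PLUS" (Sample Size and Planned Recruitment Rate).
- Length of pilot participation: up to 6 months, or 0.5 year (Overview of Study Design).

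Maximum exposure = clients × years per client = 40 × 0.5 = 20 client-years.

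This is a ceiling, since both inputs are maxima. The article gives no rate of medical emergencies, so 20 client-years cannot be turned into an expected number of events.

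**The case against.** The strongest reply is that a condensed article is being read as if it were the participant material. Clients receive their instructions from the consent form, the printed guide and the in-app list. None of these is shown, the ethics board approved the study documents, and the safety section says the consent form deals with emergent situations. The guide is summarized in one clause and may contain more than that clause says. The instruction is also qualified, so that clients use whichever resource fits, and a facility on the list might offer emergency care. Nothing suggests that the study discourages ordinary use of emergency services; the app is used in addition to standard care.

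Much of this stands as a limit on the conclusion. It cannot be shown that any client has been misdirected, and the participant documents may already be correct. It does not repair the sentence, for three reasons:

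- The qualifier lets the client choose only among the listed resources, and none is described as an emergency medical service.
- The natural reading of the facilities is mental health facilities, and a client should not have to infer otherwise during an emergency.
- The article did not leave the matter to another document. It states an instruction for a medical emergency, so that instruction should be right.

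It is also fair to say that reuse of this wording in the tool kit is a possibility and not an established fact.

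**Conclusion.** The concern holds. As written, the safety section directs clients with a medical emergency to a guide described only in mental health terms, and no other part of the article gives them a route to emergency care. The exposure is at most 20 client-years in the pilot, with no event rate available and no count of harms claimed.

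The conclusion rests on two things: that the guide is the only possible referent of the instruction, and that its one-clause description is accurate. Confidence is medium, because the consent form or the guide may already name emergency services. In that case the fault is confined to the article's wording. The point has no bearing on sample size, feasibility targets or analysis, but it should be corrected because the population's risk is acknowledged and the remedy is simple.

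**What to change.** Replace the combined sentence with two:

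1. Clients having a medical emergency are told to contact emergency health services. The section already uses this route for adverse health events during study engagements.
2. Clients who receive no PRC response through Peer PLUS, or who are in distress, are told to use the mental health resource guide.

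Then check that the consent form, the printed guide and the in-app list say the same, and change only those that do not. Carry the corrected wording into any tool kit material that covers emergencies.

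The cost is one reworded sentence and a check of three participant documents, with possibly a minor ethics board amendment if one of them needs correcting.
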